### Surgical procedure under general anesthesia: randomization (visit 1, physician 2)

Patients must be on fasting state the day of the surgery, at least 6 h prior to anesthesia for solids and 3 h for liquids. Patients will be monitored continuously, and the corresponding measurements will be recorded every 5 minutes, for the following standard safety parameters: non-invasive blood pressure measurements (NIBP; that is, systolic and diastolic blood pressures), ECG monitoring, transcutaneous measurements of arterial oxygen (O_2_) saturation and end-tidal carbon dioxide (CO_2_) concentration, from the pre-anesthetic period to the end of general anesthesia. Body temperature will be monitored continuously. Patients will be equipped with a bispectral index (BIS) monitor for the depth of anesthesia, as well as with a monitoring device for the neuromuscular relaxation on their skin covering the adductor pollicis muscle. Physician 2 will take into account the neuromuscular relaxation monitoring to determine (i) the appropriate time for the patient’s endotracheal intubation, (ii) needs of repeated bolus injection of cis-atracurium during the maintenance period and (iii) appropriate time for the anesthesia discontinuation.

A registration number in sequential numerical order in each center separately will be assigned to each eligible patient. Before induction, physician 2 will open the individual randomization envelope allocated to the patient in order to prepare all equipment required and study drugs needed during the general anesthesia. Prior to the study start, one randomization list has been pre-established on computer by the sponsor.

### Induction of anesthesia

Preoxygenation will be performed using oxygen (FiO_2_ = 1.0) in all patients.

Balanced anesthesia will be induced by the combination of intravenous injection of propofol administered at 1 to 2 mg/kg by bolus titration; intravenous injection of remifentanil administered at 0.5 μg/kg via infusion pump continuously; and for tracheal intubation, non-depolarizing neuromuscular blocking agents, that is, intravenous injection of cis-atracurium will be administered at 0.1 mg/kg once the depth of anesthesia is considered sufficient (40 ≤BIS Index ≤60). The internal cuff pressure measurements will be recorded every 5.

### Maintenance of anesthesia

The administration of xenon or sevoflurane (according to the randomized study group assigned to the patient) will be started in the automatic mode (Felix DualTM workstation; Air Liquide, Paris, France) to reach a target concentration of 60% (55% to 65%) of xenon, or 1.1% to 1.4% of sevoflurane. About 10 minutes should be sufficient to reach this target concentration. This 10-minute period will be covered with a total intravenous propofol infusion at 0.05 to 0.15 mg/kg/min.

Then, the administration of propofol will be stopped. Simultaneously the xenon or sevoflurane will be administered in the economic mode (Felix DualTM workstation) for all patients to maintain the following target concentration according to randomized study group assigned to the patient: group A: xenon 60% (55% to 65%) (1 MAC) in oxygen (FiO_2_ = 0.35 to 0.45), group B: sevoflurane 1.1% to 1.4% (1 MAC) in oxygen (FiO_2_ = 0.35 to 0.45) and medical air.

Whatever their randomized study group assigned, patients will receive intravenous injection of remifentanil via infusion pump at an initial rate of 0.15 μg/kg/min, then titrated to the clinical needs. In addition intravenous bolus injections of cis-atracurium at 0.025 mg/kg will be administered according to physician 2’s judgment.

### Monitoring throughout the anesthesia

Systolic blood pressure should be kept ≥ 100 mmHg (or ≥ 60 mmHg for mean arterial blood pressure), and a relative variation > 20% from baseline values has to be avoided by administering rescue medication. The ECG will be monitored continuously and heart rate should be kept between 60 and 100 beats per minute. The type and duration of any new spontaneous arrhythmias should be recorded as adverse events. Ventilation will be adjusted to maintain an end-tidal CO_2_ level between 36 and 45 mmHg. Body temperature will be maintained between 36.0°C and 37.0°C. Depth of anesthesia will be continuously monitored with BIS VISTATM monitoring system (Covidien, Dublin, Ireland) and should be kept in a range between 40 and 60 to maintain a sufficient depth of anesthesia. Within the last 45 minutes before the expected skin closure, no additional cis-atracurium injection shall be administered, in order to ensure sufficient spontaneous ventilation prior to extubation. In addition, administration of acetylcholinesterase inhibitors should be avoided.

### Rescue treatments

If autonomic activity (defined as sweating, salivation, flushing), somatic signs (defined as movement and swallowing), or hemodynamic signs (defined as a change in systolic blood pressure or heart rate more than 20% from baseline in the absence of hypovolaemia) become evident corrective treatments will be administered according to physician 2’s judgment.

Antihypertensive and inotropic agents are allowed if the heart rate or blood pressures indicate their necessary use. Appropriate blood and/or fluid replacement strategy is to be used according to physician 2’s judgment. Analgesia, including additional locoregional analgesia, will also be administered according to physician 2’s judgment.

### Wake up

At 10 minutes before the expected end of all surgical procedures, the inhaled anesthetic agents will be reduced to 0.5 MAC. After the effective skin closure, the Train of Four (TOF) test will be performed to exclude existing neuromuscular relaxation. From this timepoint, adequate spontaneous ventilation has to be ensured and end-tidal carbon dioxide level is allowed to increase up to 50 mmHg. Recovery parameters, namely time to open eyes, time to react on verbal command, time to extubation and time to spatial orientation, are to be recorded.

### Post-anesthesia care unit (PACU)

The patients will be transferred to the PACU (if necessary, patients will be discharged directly to intermediate care or intensive care units) for continuous vital signs monitoring (NIBP, ECG and transcutaneous measurements of arterial oxygen saturation. Every 15 minutes, the vital signs and Aldrete score will be recorded until patients are considered ready to discharge from the PACU, that is, when their Aldrete score reaches a value ≥ 9 ( 
Additional file 3: Table S2) 
[23]. Postoperative nausea and vomiting (PONV) and blood loss will be assessed. The timepoint of this last evaluation of the Aldrete score will be considered as the end time of the recovery period, that is, the time to readiness to be discharged from the PACU.

### Postoperative pain management

Once the patient is able to evaluate his/her pain on a 100-mm VAS, postoperative analgesia (including additional locoregional analgesia) will be administered according to the local procedures of each participating center, in order to maintain a VAS pain score ≤ 30 mm. The administration of oral or intravenous non-steroidal anti-inflammatory drugs (NSAIDs), as well as opioids in the regional anesthesia, will be avoided.

### PONV management

Once the patient is able to evaluate his/her nausea on a 11-point verbal rating scale (VRS, 
Additional file 4) (with 0 corresponding to no nausea and 10 corresponding to nausea as bad as it could be) 
[24], Dexamethasone 8 mg and/or a 5HT3-antagonist (such as ondansetron 4 mg administered every 6 h if necessary) will be administered if the patient is retching or vomiting or if his/her VRS for nausea is > 3; see 
Additional file 4.

### Postoperative blood and/or fluid loss management

The blood and/or fluid replacement strategy is to be used according to physician 2’s judgment.

### Follow-up visits (visits 2 to 7, physician 1)

All randomized patients will be followed up from 3 h to discharge from the hospital (or at maximum 28 days post surgery), or withdrawal from the study. The 4 days following the surgery, CAM, VAS, SOFA and laboratory results, including platelets count, serum hemoglobin, hematocrit, leucocytes, aspartate aminotransferase (AST), alanine aminotransferase (ALT), γ- glutamyltransferase, total bilirubin, serum creatinine and urea concentrations, troponin I or troponin T, C-reactive protein, serum sodium and potassium and serum glucose concentration will be recorded. From day 5 onwards, SOFA and laboratory results become optional. Vital signs, concomitant medications, adverse events and serious adverse events are obtained in all study visits. Details of the study evaluations performed are presented in Table
1.

### Evaluation criteria

The primary efficacy criterion is POD diagnosed via CAM at least once within 4 days post surgery.

The secondary efficacy criteria include: (1) POD diagnosed with the CAM from day 5 post surgery to discharge from hospital; (2) SOFA from day 1 to day 4 post surgery; (3) recovery parameters; (4) economic parameters, which are addressed to evaluate the economical impact of POD in the postoperative period from the hospital perspective; (5) safety: adverse events and serious adverse events, and laboratory parameters.

### Safety evaluations

All adverse events (AEs) occurring during the whole study period will be recorded by the investigators. Physician 1 will record all AEs apart from those occurring on the day of the surgery, between the time of admission of the patients in the operating room to the time of discharge of the patients from the PACU. The information recorded in the case report forms for each AE experienced by the patients throughout their whole study period will include the nature of the events, their onset date and time, their end date and time, their severity, the corrective treatment(s) started if applicable, the outcome of the events and their relationship to the investigational inhaled gas and to the intravenous line applied separately as assessed by the investigator who records the AE. Physician 1 will record the relationships of each AE described to the investigational inhaled gas and to the intravenous line applied separately without knowing the nature of the study drugs administered.

### Economic parameters

Time to readiness to be discharged from the operating room, effective times of admission and discharge from the operating room, onset and end times of the general anesthesia and surgical procedure (onset and end times of induction, time of intubation, onset and end times of the administration of the study treatments, time of skin incision and end of wound dressing, time of extubation), total drugs (xenon or sevoflurane) consumption per patient, are to be recorded by Physician 2, as well as the type of hip fracture surgery performed (such as total hip replacement, hemiarthroplasty of the hip, dynamic hip screw, cemented or not cemented).

### Statistical methods

The main analysis of the primary efficacy criterion will correspond to the primary objective of the study which is to evaluate the incidence of POD, diagnosed via CAM, in older patients undergoing hip fracture surgery under general anesthesia with xenon or sevoflurane, for a period of 4 days post-surgery. All data collected will be tabulated descriptively by group on the intention to treat (ITT) dataset (which will be composed of all randomized patients). The number of patients having being diagnosed POD with the CAM at least once throughout their study participation from visit 2 to visit 6 will be calculated in each group, and this number of patients will be divided by the total number of participating patients of the corresponding group. This ratio which represents the rate of POD diagnosed within 4 days post surgery will be compared between both groups, using the Pearson’s *χ*^2^ test and its calculation provided by the FREQ procedure of the current version of the SAS software (SAS, Cary, NC, USA), on the ITT dataset.

Additional analyses of the primary efficacy criterion as time elapsed between the onset of the maintenance period of the general anesthesia and the first POD diagnosis with the CAM post surgery (expressed in full number of started hours) will be tabulated by group, as both quantitative and categorical data, in the subgroup of patients for whom POD is diagnosed at least once within 4 days post surgery. Time to first POD diagnosis with the CAM post surgery will also be described globally by group, on the ITT dataset, using Kaplan-Meier estimates to display the probability of survival and of being diagnosed POD. Survival times will be censored at the time of the patients’ last contact (in the subgroup of patients for whom POD is never diagnosed within their trial participation post surgery) or at the time of the first POD diagnosis with the CAM (in the subgroup of patients for whom POD is diagnosed at least once within their trial participation post surgery). If relevant, times to first POD diagnosis with the CAM post surgery will be compared between both groups with the Log rank test.

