## Background

Postoperative delirium (POD) is an acute confusional state associated with changes in consciousness, arousal level and cognitive status characterized by inattention within 30 days after an operation 
[1] and occurs in 15 to 53% of older patients 
[1,2] particularly in those with hip fractures 
[1,3]. We have recently conducted a meta-analysis showing that delirium associated with hip fracture doubles the hazard ratio of death (HR 2.3 95% CI 1.4 to 3.9) 
[1]. Furthermore the development of delirium often initiates a cascade of events culminating in the loss of independence, poor functional recovery, and increased morbidity, as well as increases in length of hospital stay, discharges to nursing facilities, and healthcare costs 
[1-6].

The pathogenesis of delirium is poorly understood though Sanders has proposed that delirium can be considered as a ‘cognitive disintegration’ whereby the integrated neural function of the brain is broken down producing a varied range of symptoms focused on consciousness, arousal and memory 
[7]. Within the proposed framework various non-modifiable patient risk factors are hypothesized to contribute to reduced network connectivity (a surrogate for integration) at baseline, for example, age 
[7]. Modifiable risk factors (including inflammation and sedative drugs) act to further decrease network integration in the brain through altering the balance of neural transmission predominantly through increases in inhibitory tone mediated by γ-amino-butyric acid (GABA) signaling in the brain 
[7]. A prediction of this theory is that avoidance of GABAergic drugs, that include the majority of anesthetic (for example, sevoflurane or propofol) and sedative agents, would reduce the burden of postoperative and intensive care delirium.

In parallel, research showing multiple beneficial effects of the non-GABAergic anesthetic agent xenon has been published. As an inert, noble gas, xenon is not metabolized by the body but yet exerts myriad biological effects, the most notable being anesthesia and organ protection 
[8-18]. Xenon is thought to produce anesthesia through targeting either excitatory *N*-methyl-d-aspartate or two-pore-domain-potassium channels but not GABA_A_ receptors 
[8,9,13]. Xenon anesthesia is rapid onset, cadiostable and xenon is not thought to disturb autoregulation of organ blood flow 
[8,9,13]. Furthermore, xenon protects the brain, heart and kidney from diverse toxic insults including ischemia 

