### Sample size calculation

We assume an expected rate of 30.0% of POD diagnosed with the CAM at least once within 4 days post surgery on sevoflurane, see Table
2[3,25-32]. We hypothesize a reduction of 50% to a rate of 15.0% of POD on xenon. The type I error is set to be α = 0.05 (two-sided conditions) and the power (1 - β) equals 0.80. Taking the above-mentioned facts into consideration, the sample size calculation results in 121 patients per group (the estimation is based on the two-group *χ*^2^ test of equal proportions). With an expected 5.0% dropout rate over 4 days post surgery, 256 patients will be randomized in this trial, that is, 128 patients in the xenon and 128 patients in the sevoflurane group. The sample size calculation was performed using nQuery Advisor® Version 6.01 (Statistical Solutions, Saugus, MA, USA). 

**Table 2 T2:** Incidence of postoperative delirium

**Author**	**Study type**	**Patients**	**Age (years)**	**Method**	**Incidence**	**Comments**
Marcantonio E, 2001 [26]	RCT	64	>65	CAM	50%	Total (n = 126)
Marcantonio E, 2002 [27]	PCS	122	>65	CAM	40%	Subanalysis of [25]
Marcantonio E, 2002 [28]	PCS	126	>65	CAM	41%	Subanalysis of [25]
Furlaneto M, 2006 [3]	PCS	106	>65	CAM	29.1%	
Zakriya K, 2002 [29]	PCS	168	>65	CAM	28%	
Zakriya K, 2004 [30]	PCS	92	>65	CAM	28%	
Sharma P, 2005 [31]	PCS	47	>56	CAM	36%	
Galanakis P 2001 [32]	PCS	37	>60	CAM	40.5%	

This table is an excerpt from studies assessing delirium with the CAM. Based on these data the power for this study has been calculated.

CAM = Confusion Assessment Method; PCS = prospective cohort study; RCT = randomized controlled trial.

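### The primary chi-square test is valid and meets its planned 80% power, but it leaves baseline age and MMSE unused and so forgoes a possible gain in power

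*Protocol article*

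**What the plan says.** The endpoint is binary: "The primary efficacy criterion is POD diagnosed via CAM at least once within 4 days post surgery" (Evaluation criteria). Under Statistical methods, the patients with at least one positive CAM from visit 2 to visit 6 are counted and divided by the group total. Then: "This ratio which represents the rate of POD diagnosed within 4 days post surgery will be compared between both groups". The test is Pearson's chi-square from SAS FREQ on all randomized patients. No covariate or stratum is named. The additional Kaplan-Meier and log-rank analyses are described without adjustment too.

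On risk factors, the Background states that "various non-modifiable patient risk factors are hypothesized to contribute to reduced network connectivity" and gives age as the example. Table 1 and the pre-anesthetic assessment section place demographic data and MMSE at visit 0. Patients who cannot complete the MMSE are excluded, so it should be nearly complete. Eligibility is limited to age 75 or older and MMSE of 24 or above.

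On centre, the section on randomization (visit 1) describes one list prepared by the sponsor and names no stratification factor. It adds: "A registration number in sequential numerical order in each center separately will be assigned to each eligible patient". Postoperative analgesia "will be administered according to the local procedures of each participating center".

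The Sample size calculation section fixes the planning values: "We assume an expected rate of 30.0% of POD diagnosed with the CAM at least once within 4 days post surgery on sevoflurane". This rate is halved to 15% for the xenon arm, with a two-sided 5% level and 80% power. It arrives at 121 per group by the two-group chi-square test, and at 256 in total after 5% dropout.

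**The concern.** Adjusting for baseline variables that truly predict a binary outcome raises the power to detect a treatment effect and corrects for chance imbalance in those variables. Here two candidate variables are collected anyway, and the article describes neither stratification nor covariate adjustment that would use them. The trial is planned at 80% power, and the Discussion reports inclusion about 50% slower than expected. Any precision obtainable without extra patients is therefore worth having. At stake is the efficiency of the primary comparison, not its validity.

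**Working it through.** **1. The plan's own figure.** Inputs from the Sample size calculation section: p₁ = 0.30, p₂ = 0.15, two-sided α = 0.05, power 0.80. The mean rate is 0.225.

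n = [1.960·√(2·0.225·0.775) + 0.842·√(0.30·0.70 + 0.15·0.85)]² / 0.15²

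= [1.960·0.5906 + 0.842·0.5810]² / 0.0225 = (1.1575 + 0.4889)² / 0.0225 = 120.5, rounded up to 121.

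Dropout: 121/0.95 = 127.4, rounded up to 128 per group, or 256 in total. Both stated figures reproduce.

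**2. Power of the unadjusted test at 121 per group.**

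z = (0.15·√121 − 1.1575)/0.5810 = (1.650 − 1.1575)/0.5810 = 0.848, which gives 80.2%.

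With all 128 per group evaluable, the same formula gives 82.4%. The planned power is met by the planned test.

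**3. What adjustment could add.** The article gives no prognostic strength for any baseline variable, so a range was assumed. Each scenario simulated 3,000 trials with 121 per group and 10 centres, holding the marginal rates at 30% and 15%. Age and MMSE were independent standard normal variables with the log-odds slopes shown, and centre was a normal effect with the SD shown. The unadjusted chi-square test was compared with the likelihood-ratio test for arm in a logistic model. The AUC is that of age, MMSE and centre combined.

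| Slopes for age, MMSE; centre SD (assumed) | AUC | Unadjusted | Age + MMSE | Age + MMSE + centre |
|---|---|---|---|---|
| 0, 0; 0 | 0.50 | 80.9% | 80.9% | 80.3% |
| 0.25, 0.25; 0.2 | 0.61 | 80.5% | 81.4% | 80.6% |
| 0.4, 0.5; 0.3 | 0.68 | 81.2% | 83.0% | 84.0% |
| 0.6, 0.7; 0.5 | 0.75 | 80.9% | 85.1% | 86.7% |
| 0.8, 0.9; 0.6 | 0.80 | 80.6% | 87.2% | 88.3% |

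The Monte Carlo standard error is √(0.81·0.19/3000), about 0.7 point per figure. The change from age and MMSE alone is 0.0, +0.9, +1.8, +4.2 and +6.6 points. The second value is little more than one standard error of a single figure and is best read as nil. Adding centre as fixed effects changes power by −0.6, +0.1, +2.8, +5.8 and +7.7 points against the unadjusted test.

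**4. Type I error.** With 30% in both arms and AUC 0.68, rejection rates were 4.8% unadjusted, 4.9% with age and MMSE, and 5.4% with centre added (standard error about 0.4 point). All are compatible with 5%.

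**5. How large a model the data can carry.** Expected events are 121·0.30 + 121·0.15 = 36.3 + 18.15, about 54. Arm, age and MMSE are three terms, about 18 events each. Fixed effects for 10 centres make 12 terms, about 4.5 events each. For 13 centres, counting the three to be added, there are 15 terms and about 3.6 events each.

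**The case against.** The strongest case for leaving the plan alone is that nothing in it is in error. The unadjusted test is valid under 1:1 randomization, no stratification factor is stated that the analysis would have to respect, and the sample size was computed for this same test. Chance imbalance in age or MMSE is already allowed for in the test's type I error. Eligibility truncates both covariates, which may leave them little to predict. Changing the primary analysis after 121 of 256 patients have been randomized is a real amendment. Adjusted supportive analyses may also sit in an analysis plan that is not shown. All of this stands. It limits the point to an efficiency recommendation but does not remove it, because the article itself fixes the primary test.

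Three stronger readings are tempting, and the document supports none of them.

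- A reader might infer that the trial falls short of its power. It does not, as step 2 shows.
- A reader might infer that age, MMSE and centre are all expected to drive delirium. Only age is named as a risk factor. For MMSE the support is indirect: the Discussion ties the cognitive exclusions to being able to show efficacy. For centre there is only local analgesic practice, under a common pain target and a common avoidance of NSAIDs. Numbering patients by centre says nothing about prognosis.
- A reader might turn the gain into recruitment, for instance 8 to 20% more patients if a single baseline score is given an AUC of 0.66 to 0.77. That range has no source in the document.

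**Conclusion.** The point holds as a suggestion for better efficiency. Adjusting for age and MMSE would give about 81% to 87% power where the unadjusted test gives about 81%, a gain of nil to between 6 and 7 points. It was not below the unadjusted test in any scenario examined. The direction is secure if the covariates are prognostic. The size is not, because it rests on assumed slopes, on independent and normally distributed covariates, and on the plan's rates of 30% and 15%. If age and MMSE are weak predictors within the enrolled range, the gain is nil. Centre does not belong in the primary model on this evidence: it is not a stated stratification factor, and about 54 events are few for 10 to 13 centre effects.

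**What to change.** Before any unblinding, amend the protocol and analysis plan as follows.

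- Make the primary analysis a logistic regression of POD (visits 2 to 6) on arm, age and baseline MMSE, with both covariates continuous.
- Name the one test of the arm term that decides the result. The figures above used the likelihood-ratio test.
- Report the standardized risk difference with its 95% confidence interval, which keeps the comparison on the scale of the two rates, together with the odds ratio.
- Keep the Pearson chi-square test as a supportive analysis.
- If centre is to be examined, do so in a sensitivity analysis only, as a random intercept or as pooled strata with the pooling rule set in advance.

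The cost is an amendment during recruitment and a slightly more complex primary analysis. No new measurement and no change in sample size is needed.

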**Figure 1 F1:**
[figure not shown]
**Study flow chart of the Hip Fracture Surgery in Elderly Patients (HIPELD) study.** V = visit; d = day; hrs = hours, GA = general anesthesia.

Physician 1 will perform visits 0, 2, 3, 4, 5, 6, 7 and 8, which includes selection of patients, follow-up visits and study end visit. Physician 1 will be kept blinded regarding the natures and doses of all study drugs administered throughout the study (Table
1 and Figure
1).

**Table 1 T1:** Study evaluations

	**Visit 0**^**a**^**(selection)**	**Visit 1**^**b**^ (**GA)**	**Visit 2**^**a**^**(3 h post GA)**	**Visit 3**^**a**^**(day 1)**		**Visit 4**^**a**^ (**day 2)**		**Visit 5**^**a**^ (**day 3)**		**Visit 6**^**a**^ (**day 4)**		**Visit 7**^**a**^ (**day 5 to D)**		**Visit 8**^**a**^ (**study end)**
				**A**	**B**	**A**	**B**	**A**	**B**	**A**	**B**	**A**	**B**	
Signed informed consent	X													
Selection criteria	X													
Demographic data	X													
Vital signs	X	X	X	X		X		X		X		X		
Medical and surgical history	X													
Concomitant diseases	X													
Concomitant medication	X	X	X	X	X	X	X	X	X	X	X	X	X	X
MMSE evaluation	X													
Randomization			X											
General anesthesia			X											
Blood sample	X			X		X		X		X		According to investigator’s judgment		
CAM evaluation	X		X	X	X	X	X	X	X	X	X	X	X	
Pain VAS evaluation	X	X	X	X		X		X		X				
Verbal Rating Scale for Nausea		X	X	X										
SOFA	X			X		X		X		X		According to investigator’s judgment		
Recovery parameters		X												
Adverse events		X	X	X	X	X	X	X	X	X	X	X	X	X

A represents 10:00 am ± 30 minutes; B represents 6:00 pm ± 30 minutes; day 5 to D is post-surgery day 5 until discharge from hospital (or at maximum 28 days post surgery), or withdrawal from the study.

^a^Physician 1; ^b^Physician 2.

CAM = Confusion Assessment Method; GA = general anesthesia; MMSE = Mini-Mental State Examination; SOFA = Sequential Organ Failure Assessment; VAS = visual analog scale.

Physician 2 will perform visit 1, which includes randomization and surgical procedure under general anesthesia.

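### Beyond day 4, the Kaplan-Meier curve for time to first POD censors discharge and death, so it overstates the probability of being diagnosed in the trial

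*Protocol article*

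**What the plan says.** The Statistical methods section adds a time-to-event description to the primary comparison. On the intention-to-treat set, time to first POD diagnosis is shown by group "using Kaplan-Meier estimates to display the probability of survival and of being diagnosed POD". If relevant, a log-rank test follows.

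The rule for undiagnosed patients is to stop the clock at last contact, "in the subgroup of patients for whom POD is never diagnosed within their trial participation post surgery". The reference is to the whole trial participation, not to the four days of the primary criterion. No separate rule is given for death.

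The end of observation is set elsewhere. Under Follow-up visits, patients are "followed up from 3 h to discharge from the hospital (or at maximum 28 days post surgery), or withdrawal from the study". The footnote to Table 1 defines the last period with CAM assessments: "day 5 to D is post-surgery day 5 until discharge from hospital (or at maximum 28 days post surgery), or withdrawal from the study". Table 1 has no CAM at visit 8. Diagnoses after day 4 are expected, because one secondary criterion is "POD diagnosed with the CAM from day 5 post surgery to discharge from hospital".

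**The concern.** The curve is labelled as the probability of being diagnosed. Kaplan-Meier treats a censored patient as someone who could still be diagnosed later, at the rate seen in those who remain. That is reasonable for a withdrawal. It does not fit a patient who has gone home, because CAM assessment has ended, or one who has died. For diagnosis by CAM within the trial, discharge and death without POD are competing events.

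At stake is a secondary display. Its tail would show more POD in each arm than the trial observed over the same stay, and it would rest on the few patients with long stays.

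**Working it through.** **The plan's own figure.** For 30% versus 15%, two-sided α = 0.05 and power 0.80:

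n = [1.960·√(2·0.225·0.775) + 0.842·√(0.30·0.70 + 0.15·0.85)]² / 0.15² = 120.5, so 121 per group.

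121/0.95 = 127.4, so 128 per group. The stated size reproduces and does not depend on the censoring rule.

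**Direction of the error.** Let N be the arm size, Y the number at risk just before a diagnosis and S the Kaplan-Meier estimate at that time. One diagnosis raises the proportion diagnosed by 1/N and raises one minus Kaplan-Meier by S/Y. If nobody has left undiagnosed, Y = N·S and the two steps are equal. Each discharge or death without POD lowers Y but not S, so S/Y then exceeds 1/N.

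**An example with whole patients (illustrative counts).** Of 128 patients, 38 are diagnosed by day 4. Of the other 90, 60 leave; one of the remaining 30 is diagnosed; 20 more leave; one of the remaining 9 is diagnosed.

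- One minus Kaplan-Meier: 1 − (90/128)(29/30)(8/9) = 39.6%.
- Proportion diagnosed: 40/128 = 31.3%.

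Two late cases open a gap of about 8 points.

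**Size under assumptions.** The document gives 30% (sevoflurane) and 15% (xenon) by day 4, and 128 per arm. It gives no length of stay, late hazard or death rate. These are assumed here: first-POD hazard h of 0 to 2% per in-hospital day after day 4; discharge of 7%, 10% or 15% per day after day 4 (the last with 5% also on each of days 3 and 4); death 0.2% per day. Withdrawals are set to zero, so that the gap comes only from discharge and death.

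At day 28, one minus Kaplan-Meier is 1 − 0.70·(1 − h)^24. For h = 1% this is 1 − 0.70·0.786 = 45.0%.

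The proportion diagnosed is 30.0% plus (Y₄/128)·h·(1 − s^24)/(1 − s). Here Y₄ is the number at risk after day 4 and s = (1 − h)(1 − discharge − death). For h = 1% and 10% discharge, Y₄ = 88.9 and s = 0.99·0.898 = 0.889. The addition is (88.9/128)·0.01·8.48 = 5.9 points, giving 35.8% (from unrounded values).

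| Day 4 rate | Late hazard per day | 1 − KM, day 28 | Proportion diagnosed, day 28 | Gap (points) |
|---|---|---|---|---|
| 30% | 0 | 30.0% | 29.8–30.0% | 0–0.2 |
| 30% | 0.5% | 37.9% | 31.8–33.8% | 4.1–6.1 |
| 30% | 1% | 45.0% | 33.7–37.4% | 7.6–11.3 |
| 30% | 2% | 56.9% | 37.2–43.7% | 13.2–19.7 |
| 15% | 0.5% | 24.6% | 17.3–19.7% | 4.9–7.3 |
| 15% | 1% | 33.2% | 19.6–24.0% | 9.2–13.6 |

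**At day 4.** With 10% discharged on each of days 3 and 4, the figures are 30.0% and 29.7%, a gap of 0.3 points.

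**Death alone.** With no discharge, h = 1% and death at 0.2% to 0.5% per day, the day-28 gap is 0.5 to 1.2 points. Discharge therefore accounts for nearly all of it.

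**The case against.** The strongest objection concerns the target. The Background defines POD as arising within 30 days of an operation, with no in-hospital limit. For delirium wherever it occurs, discharge ends observation and not risk, so censoring there is ordinary. The open question would then be whether leaving is informative, which a cumulative incidence curve does not solve. This stands as a question of estimand. But the article names diagnosis with the CAM, and the trial makes that diagnosis only until discharge. For that quantity the curve is mislabelled.

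Second, the Discussion says POD falls mainly in the first four days and plateaus afterwards. The late hazards are assumptions, and 2% per day has no source in the document, so the lower rows deserve more weight. This stands.

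Third, the display is descriptive, and an article may leave detail to an analysis plan. The first part is right and limits the importance. The second does not answer the point, because the censoring rule and the label are both stated.

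Three stronger inferences are tempting and are not supported:

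- That the curve will contradict the trial's crude POD rate. The rate defined in Statistical methods covers visits 2 to 6, to day 4, where the gap is negligible.
- That only Kaplan-Meier is affected by discharge timing. With equal, non-informative POD hazards the reverse holds: at 1% per day Kaplan-Meier stays at 45.0% whatever the discharge rate, while the cumulative incidence moves between 33.7% and 37.4%.
- That one late case among as many as 10 at risk moves the curve by 10 points or more. With 30% diagnosed by day 4, S is at most 0.70, so the step is at most 0.70/10 = 7 points.

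**Conclusion.** The point holds as a correction to a secondary display. Beyond day 4, one minus Kaplan-Meier under the stated rule does not estimate the probability of being diagnosed in the trial. The direction of the error needs no assumption about hazards or stays, only that some first diagnosis follows another patient's discharge or death without POD.

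The size does rest on assumptions. At day 28, with late hazards of 0.5% to 1% per day, the gap is about 4 to 11 points at the sevoflurane rate and 5 to 14 at the xenon rate. It is close to zero if there are no late diagnoses. Two readings of the text are also assumed: that death falls under last contact, and that diagnosis is meant as the event. The article literally says that diagnosed patients are censored "at the time of the first POD diagnosis with the CAM (in the subgroup of patients for whom POD is diagnosed at least once", which would leave no events.

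A reader might infer that the trial's main result or its log-rank test is invalid. The documents do not support that. The primary chi-square test and sample size do not use the rule, and the log-rank test remains a valid comparison of in-hospital cause-specific hazards.

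**What to change.** Replace the Kaplan-Meier display by the cumulative incidence (Aalen-Johansen) of first CAM-diagnosed in-hospital POD by arm. Treat discharge alive without POD and death without POD as competing events. Censor only withdrawals and patients still in hospital at day 28. Alternatively, end the Kaplan-Meier display at day 4, the window of the primary criterion.

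State that first diagnosis is the event. Keep the log-rank test, labelled as a comparison of in-hospital cause-specific hazards, and print numbers at risk under the curves.

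The cost is analysis-plan wording and a standard SAS option; the discharge date is already needed to define the end of follow-up. There are two downsides. The displayed probabilities will be lower, and the cumulative incidence also reflects any difference in length of stay between arms, so it should be read beside the cause-specific comparison. Stopping at day 4 avoids this but leaves later diagnoses off the curve.
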